***d) Procedures***

*Sponsor, steering and monitoring committees*

The trial sponsor will be the University of Oxford. The sponsor will be responsible for ensuring appropriate arrangements are in place for the initiation, management and financing of the trial, the trial is conducted to a high scientific quality and the rights of participants are protected. A trial steering committee (TSC) will be appointed to oversee the running of the trial. A data safety and monitoring committee (DSMC) will be convened. The focus of the DSMC is safety, the overall integrity of the study, and its continued relevance and ability to answer the primary objective. The TSC will be advised on the study progress and continuation by the DSMC. One interim unblinded analysis will be conducted by the DSMC during the trial after 50% of participants are recruited. A recommendation to the sponsor to discontinue recruitment, in all patients or in selected subgroups, may be made by the TSC on advice from the DSMC if the data provide proof beyond reasonable doubt that one of the treatment arms is better in terms of the primary outcome or safety guided by the Haybittle-Peto criteria. A local safety monitor (LSM) will be appointed to provide independent consultation on clinical care, management of clinical cases. The LSM will also retain a sealed code break envelope and in may be able to un-blind specific individual allocation if required for safety considerations.

*Training and setting up*

At each site an initial period will be spent training staff in anthropometry and management of severe malnutrition in order that children will be managed in line with WHO recommendations to the best standard available at each hospital. This will be followed by study-specific training. Staff at all sites will be trained on the background to the trial; scientific and ethical aspects of clinical research and trials; ICH GCP; anthropometry; data collection; communication and consenting procedures.

*Screening*

The screening process will be based on the severe malnutrition criteria which is part of routine hospital admission procedure for all children, as specified in national guidelines for care of severe malnutrition.

*Enrolment*

Enrolment will occur at the time that F75 milk would normally be started. Details of the study will be communicated to the parents/guardians of potential participants. Prior to seeking informed consent, information on benefits and risks will be provided to parents or carers in their local language and written informed consent sought. In order to ensure patients receive optimal care, to avoid delaying urgent feeding (i.e. as per WHO recommendations to prevent hypoglycaemia), assent for participation will be sought, and then written consent requested after the initial stabilisation. In the rare event that a child for whom assent for participation has been given, but who dies before written consent has been given, data and samples will be used for the study but parents and caregivers will not be asked for written consent at this time of grief. This approach is being successfully used in another study SSC#1778.

Baseline data of prognostic importance will be collected, including vaccination status. A blood sample for haemoglobin and storage of plasma, will be collected at enrolment (up to 5ml, not exceeding 1ml/kg body weight).

*Investigational product*

We will evaluate the effect of a lactose free, reduced carbohydrate F75 compared to standard F75:

1. F75 with 63% of total energy from carbohydrates, including 10% of energy from lactose (standard F75).

2. F75 with 43% of total energy from carbohydrates, without any lactose, and providing the same amount of energy as standard F75 by increased lipid in the form of medium chain triglycerides.

Although increasing energy from lipids to 52% could potentially result in some fat malabsorption leading to steatorrhoea, it will not cause osmotic diarrhoea. Steatorrhoea does not cause severe dehydration and electrolyte imbalances. In the standard RUTF that currently used in severely malnourished children, the energy content provided by lipids is ~60%, which is well tolerated in this patient group.

Standard F75 and reduced carbohydrate F75 will be manufactured to GMP standards by Nutriset®, France who are the current supplier to UNICEF and the Kenyan and Malawian national programmes, and through these channels, to the study hospitals. Protein and micronutrient components will be unchanged and taste is very similar. The study products will be identically packaged, marked ‘for research use only’. Dosing will be as per Kenyan and Malawian recommendations: 130 kcal/kg/day per day, divided into 8 feeds per 24 hours.

|  | % Energy | | Quantity: g/1000ml | |
| --- | --- | --- | --- | --- |
|  | **Standard F75** | **Modified F75** | **Standard F75** | **Modified F75** |
| Protein | 5.3% | 5.3% | 9.9 | 9.9 |
| Lipid | 31.5% | 51.7% | 26.3 | 43.1 |
| Carbohydrate | 63.2% | 43.0% | 118.5 | 80.6 |
| **Total** | **100%** | **100%** | **154.7** | **133.6** |
|  |  |  |  |  |
| Lactose | 9.9% | 0% | 18.6 | 0 |
| Sucrose | 3.6% | 3.6% | 6.8 | 6.8 |
| Maltodextrin | 50% | 39% | 93.2 | 73.9 |

*Formulations of standard F75 and modified F75*

*Randomisation*

Sequential study numbers will be generated for each site according to a prepared blocked randomisation list of random block sizes before the study begins. Randomisation codes linking allocation to study number will be held by the local safety monitor and chair of the DSMC be opened only in case an individual safety concern or until the database is unlocked. Children will be allocated study numbers sequentially within each site, thus randomly allocating the intervention and maintaining blinding. Group allocation will remain unknown to participants and trial personnel, including the trial-coordinator and principal investigator. Code breaks will be provided to the research team, to be used only in the case of an emergency; 24 hour access will be provided to these code breaks by mobile phone.

*Clinical care*

Children will be managed to the best standard available in each facility, in line with the Kenyan and WHO recommendations. HIV testing by rapid antibody test is routinely offered by the hospitals involved in the trial at admission to all severely malnourished children through ‘provider initiated testing’ according to the current National Guidelines for HIV Testing and Counselling in Kenya (2008) and appropriate follow up tests and referral for care are undertaken according to the results.

*Follow up*

Children will be examined daily whilst in hospital and clinical status recorded on a standardised proforma (appendix d). A blood sample and stool sample will be taken at day 3 to assess for metabolic effects of refeeding and carbohydrate malabsorption. If children deteriorate during the transition phase or phase 2 and are placed back on phase 1, they will receive the same F75 intervention diet as allocated during the initial treatment. The decision to discharge will be made by the usual clinical team rather than trial personnel. Food supplements and/or nutritional counselling and follow up in the nutritional clinic that are the current standard of care at each institution will also be done at discharge. No study follow up after discharge will be done.

[figure not shown]

*Outcome measures*

*Primary outcome:* the choice of primary outcome is based on the therapeutic purpose of F75, which is to achieve stabilisation and thereby allow a child to progress to feeds with higher protein and energy content to enable catch-up growth.

The primary outcome is stabilisation, defined as having reached the second (transition) phase of treatment. The criteria for stabilisation will be according to WHO guidelines:

Absence of any WHO danger or emergency signs: obstructed breathing, respiratory distress, cyanosis, shock (delayed capillary refill plus fast & weak pulse plus temperature gradient), severe anaemia (Hb<5g/dl), congestive cardiac failure, impaired consciousness, convulsions, severe dehydration, profuse watery diarrhoea, vomits everything, hypothermia.

*and*

If there is oedema at baseline, loss of oedema defined as improving from a severe +++ oedema (severe: generalized bilateral pitting oedema including feet, legs, arms and face) to ++ oedema (moderate: no upper arm or upper leg oedema and no facial oedema or from ++ oedema to + (mild: only feet/ankle oedema) or none;

*and*

Tolerating full prescribed volume of F75 feeds and observed to be completing the feeds.

For analysis, children who die before stabilisation will be classified as ‘not transitioned’.

*Pre-specified secondary outcomes*:

1. Number days with diarrhoea (3 or more loose stools within 24h);
2. Number days requiring rehydration fluids (ReSoMal or IV fluids);
3. Percentage change in weight between admission and day 5;
4. Changes in sodium, potassium, magnesium, calcium, phosphate and albumin between admission and day 3;
5. Faecal electrolytes, pH and fat at day 3;
6. numbers of episodes of ***new onset*** severe clinical deterioration accompanied by one or more of the following features: shock (fast and weak pulse and limb versus core temperature gradient and capillary refill time>3 seconds), respiratory distress (subcostal chest wall indrawing, hypoxaemia (SaO_2_) or requiring oxygen); impaired consciousness (Blantyre coma score<4) or hypoglycaemia (<3.0 mmol/l);
7. mortality until discharge;
8. time to discharge from hospital in days;
9. total days spent in the stabilization phase, including periods when the child may go back to the stabilization phase during a deterioration;
10. the proportion children with a diarrhoeal pathogen detected, (see laboratory procedures on page 8).
11. Exploratory analysis of plasma and faecal markers of gut inflammation and permeability (see laboratory procedures on page 8).
12. Gut microbiome (see laboratory procedures on page 8).
13. Metabolite profiles in plasma and stool (see laboratory procedures on page 8).

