**4) Introduction**

Admission to hospital with complicated severe acute malnutrition (SAM) in Africa commonly has a case fatality of 10-30%.[^1-3^](#_ENREF_1) Importantly, children are usually admitted to hospital because they are severely ill rather than for malnutrition alone. Mortality may be improved to some extent by adherence to WHO recommended management,[^1^](#_ENREF_1)^,^[^2^](#_ENREF_2) but the direct application of these guidelines to all contexts is controversial.[^4^](#_ENREF_4) The WHO guidelines were designed on the basis of historical data on nutrient requirements and medical treatments and almost none of the recommendations are supported by evidence from clinical trials.

For the treatment of complicated inpatient SAM, the guidelines consist of three distinct phases of treatment:[^5^](#_ENREF_5) phase 1 or stabilization phase where a low protein, liquid diet (F75) is introduced with a reduced energy intake (80-100 kcal/kg/day). Once a child has stabilised, there is a ‘transition phase’ consisting of either ready to use therapeutic foods (RUTF) with supplemental F75 or alternatively another milk formula known as F100. RUTF is a peanut based, energy dense supplement used to obtain catch-up growth. F100 is a liquid formula with a higher energy density and protein content than F75. The caloric intake is increased daily to a maximum of 130 kcal/kg/day. Finally, ‘Phase 3’ is the recovery phase during which the aim is to achieve catch-up growth with either RUTF or F100.

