***c) Sampling***

Children admitted with severe malnutrition, defined by anthropometry according to WHO guidelines, will be recruited at CPGH, Mombasa, Kilifi County Hospital and Queen Elizabeth Central Hospital (QECH), Blantyre, Malawi.

*Sample size calculation*

Based on clinical data from the actual sites, we have observed that around 50% of patients to have transitioned to the second phase of treatment by day 5. We aim for a 10% absolute increase in percentage transitioned at day 5 to 60%, which gives a hazard ratio of 1.35. Sample size for survival time was calculated using the *stpower* command in Stata version 12. Using α=0.05, 80% power, the number of patients required to demonstrate a hazard ratio of 1.35 is 381 per arm. We will aim at 420 per arm to allow for contingencies. It is anticipated that 400 children will be enrolled at CPGH, 120 at KCH and 320 at QECH. However, these figures will be adjusted in line with actual recruitment.

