***Monitoring of adverse events***

This group of children are expected to have a high frequency of adverse events regardless of this intervention. There is no specific toxicity profile associated with F75 milk. The study team will monitor children through daily clinical examination. Laboratory tests including a full blood count, electrolytes, blood glucose and liver function tests will be done as guided by requirements for clinical care. Serious adverse events, include events that are life-threatening or prolong hospital admission are pre-specified as secondary endpoints number vi) and vii) above. These will be recorded and entered on the trial database. A summary of serious adverse events will be reported quarterly, and examined in an un-blinded analysis by the DSMB at the trial mid-point and again at the end of the trial.

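### Deaths are compared by arm only once during the trial, and the stopping guide at that look is as strict for harm as for benefit, so a large mortality excess can pass it when background mortality is near 10%

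*Protocol*

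**What the plan says.** The number of looks and the stopping standard are both in section 8, d) Procedures, under the heading on sponsor, steering and monitoring committees. The protocol plans: "One interim unblinded analysis will be conducted by the DSMC during the trial after 50% of participants are recruited". A recommendation to discontinue recruitment may follow if there is near-certain evidence that "one of the treatment arms is better in terms of the primary outcome or safety guided by the Haybittle-Peto criteria". One standard therefore serves both purposes. No numerical threshold is given, and there is no separate guideline for harm.

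The section on monitoring of adverse events agrees on timing. It says "A summary of serious adverse events will be reported quarterly", without saying that the summary is by arm or who receives it. The events are to be "examined in an un-blinded analysis by the DSMB at the trial mid-point and again at the end of the trial". I take DSMB and DSMC to be the same committee.

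Under Randomisation, the allocation codes are held by the local safety monitor and the committee chair. They may be opened only for a safety concern about an individual child or once the database is released. A single code break is not a comparison between arms.

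The Introduction says that hospital admission with complicated severe acute malnutrition in Africa "commonly has a case fatality of 10-30" per cent. Mortality until discharge is secondary outcome 7.

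**The concern.** Haybittle-Peto limits are deliberately extreme so that benefit is not claimed early and the final significance level is almost untouched. That reasoning does not carry over to harm, where waiting for near-certainty exposes more children. Applied to deaths at a single look, such a limit can let a clinically large excess through, and the protocol schedules no later comparison by arm until the trial has ended.

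Two things are at stake. The first is the safety of participants in a population with high background mortality. The second is interpretation: the rule lists the primary outcome and safety as alternatives and does not say how mortality enters a decision to stop for faster stabilisation. Such a stop would leave the mortality evidence at about half its planned size, in a trial intended to change global recommendations.

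**Working it through.** **Inputs from the protocol.** Target sample size: "We will aim at 420 per arm to allow for contingencies" (c) Sampling). One look at 50% recruitment (d) Procedures). Case fatality 10-30% (Introduction).

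**Assumptions.** The look has 420/2 = 210 children per arm, all with outcome known. Haybittle-Peto is read as z=3, or as two-sided p<0.001 (z=3.29). Deaths are compared with a pooled two-proportion z test. Control mortality is 10, 15, 20 or 30%.

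**The plan's own figure.** The protocol states: "Using α=0.05, 80% power, the number of patients required to demonstrate a hazard ratio of 1.35 is 381 per arm". Freedman's formula for events is (1.960+0.842)² × (HR+1)²/(HR−1)². With HR = ln 0.5/ln 0.6 = 1.357 it gives 343 events. With 45% of children having the event, 343/0.45/2 = 381 per arm, which matches. This only confirms the scale of the trial; nothing below depends on it.

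**Deaths before the first comparison by arm.** 420 × 0.10 = 42 to 420 × 0.30 = 126, if the quoted case fatality applies to the children in the trial.

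**Death counts needed to cross.** z = (d₂−d₁)/210 ÷ √[p̄(1−p̄) × 2/210], with p̄ = (d₁+d₂)/420. Take an observed doubling at 10%, 21 v 42 deaths: p̄ = 63/420 = 0.15, the standard error is √(0.15 × 0.85 × 2/210) = 0.0348, and z = 0.10/0.0348 = 2.87 (p=0.004). It crosses neither threshold. The smallest counts that cross are:

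| Control deaths of 210 | Other arm, z=3 | Other arm, z=3.29 | Risk ratio |
|---|---|---|---|
| 21 (10%) | 44 | 46 | 2.1 to 2.2 |
| 32 (15%) | 58 | 60 | 1.8 to 1.9 |
| 42 (20%) | 70 | 72 | 1.7 |
| 63 (30%) | 93 | 96 | 1.5 |

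**Probability of crossing.** Sum of Bin(x; 210, p) × Bin(y; 210, RR·p) over all pairs (x, y) at or beyond the threshold, by exact enumeration:

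| Control mortality | Doubling, z=3 (3.29) | 1.5-fold, z=3 (3.29) |
|---|---|---|
| 10% | 45% (34%) | 7% (4%) |
| 15% | 76% (66%) | 15% (9%) |
| 20% | 94% (89%) | 26% (18%) |
| 30% | over 99% | 57% (46%) |

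**A softer guideline at the same look.** For 10% v 20%, the probability of crossing is about 83% at z=1.96 and about 62% at z=2.576.

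**Price of a softer guideline at repeated looks.** I simulated test statistics with no true effect at equally spaced looks. One-sided p<0.025 in one direction gives a false alert in about 6% of trials with 4 looks and 8% with 6. Applied to an excess in either arm, the figures are about 13% and 15%. A stricter trigger, z=2.576 in either direction, gives about 3% and 4%.

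**The case against.** The strongest reply is that one interim under a symmetric Haybittle-Peto guide is a recognised design, chosen here for a feed that the protocol considers low risk. The rule is permissive: it guides a recommendation that may be made, so the committee can act on weaker evidence. A charter, not shown, may add looks. This stands in part. Nothing in the protocol is contradictory, and crossing probabilities treat a guide as a hard limit. But judgement needs data by arm, and the protocol schedules these only once while children are still being recruited.

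A reader might infer four stronger things that the documents do not support:

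- That harm must reach the boundary before anyone can act. The wording leaves discretion.
- That a doubling of mortality would usually be missed. That is so only near 10% control mortality; from 15% upwards a doubling crosses more often than not under either threshold.
- That the rule costs 42 deaths. With 10% v 20%, the whole-trial excess is 420 × 0.10 = 42, but 210 × 0.10 = 21 of these belong to the children recruited before the look. Missing the boundary there concerns at most the other 21.
- That the trial could stop for benefit with mortality unseen. Serious events, including deaths, are reviewed unblinded at the same mid-point, safety is a named focus of the committee, and children who die before stabilisation count as not stabilised in the primary analysis. What is missing is a written requirement to weigh mortality in that decision.

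**Conclusion.** The point holds in a limited form and should be addressed. The protocol fixes a single comparison of deaths and serious events by arm during the trial and gives harm the same extreme guide as benefit. At 10% control mortality, a true doubling is more likely to pass that look than to cross. At 10-20%, a true 1.5-fold excess crosses in about a quarter of trials at most. At 20% or more, a doubling would usually be caught.

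These figures rest on the assumed threshold and on all 420 children having a known outcome at the look. Children still in hospital at that time would lower the chance of crossing. They describe the statistical guide, not what the committee would in fact decide.

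**What to change.** 1. **Monitoring of adverse events:** send the quarterly summary of deaths and severe deteriorations to the committee as a confidential closed table by arm.
2. **Randomisation:** amend the restriction on opening the codes so that they may be used for these tables. As worded, it does not provide for the planned mid-point analysis either, so one change covers both.
3. **d) Procedures:** keep Haybittle-Peto for benefit on the primary outcome. Add a less extreme mortality guideline for excess deaths in either arm, since the protocol's own rationale is that the standard feed may cause harm. The guideline should prompt a documented committee review rather than automatic stopping, and the protocol should state the looks at which it applies.
4. **Same section:** state that any recommendation to stop for faster stabilisation must take mortality by arm into account.

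The cost is short amendments to three sections, matching charter text and an unblinded person to prepare the closed tables. Blinding of trial staff is kept and no efficacy alpha is spent. The real downside is more false safety alerts, of the size shown in the working: a softer trigger at more looks raises more of them, a stricter one fewer. Because the guideline leads to review and not to stopping, the committee's judgement can absorb them.

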**3) Summary**

Inpatient treatment for complicated severe acute malnutrition (SAM) continues to have a high mortality in Africa. This is partly because children are commonly brought for admission because they are seriously ill, rather than being brought to hospital because of malnutrition alone. Mortality rates are especially high where SAM is complicated by HIV or TB. The early phase of inpatient nutritional treatment for severe acute malnutrition is based on a low-protein milk known as F75, which is given to improve metabolic homeostasis prior to the re-feeding to achieve catch-up growth. F75 provides a high proportion of energy from carbohydrates, including sucrose, lactose and maltodextrin. However, malabsorption of different types of carbohydrates, but lactose in particular, is known to occur in SAM and may lead to osmotic diarrhoea. Diarrhoea is common in children with SAM and is associated with increased mortality. Furthermore, switching from a catabolic state to a high energy diet that consists of predominantly carbohydrates can lead to ‘re-feeding syndrome’ that may lead to severe electrolyte abnormalities and multiple organ dysfunction.

The aim of this trial is to determine whether reducing the carbohydrate content of F75, and removing lactose, improves the stabilisation of severely malnourished children. The trial will involve randomising children who are eligible to receive F75 milk to either the current formulation or a revised formulation. Both formulations will be given according to current recommendations regarding frequency of feeding and caloric value. Since the purpose of F75 is to stabilise the child metabolically and biochemically, the primary endpoint of the trial will be time to stabilisation (the end of the first phase of treatment for severe acute malnutrition). Blood and stool samples at admission and after three days will be used to determine the effects on carbohydrate and fat malabsorption and evidence of the re-feeding syndrome. Children will be followed up until discharge from hospital. The project has been planned in consultation with the World Health Organisation (WHO) and, if the revised formulation of F75 results in improved outcomes, will lead to a global change in recommendations for its formulation.

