Apart from diarrhoea, early deterioration may also be related to severe metabolic derangements due to a sudden change from a catabolic to an anabolic state, resulting in refeeding syndrome.[^15^](#_ENREF_15) Refeeding syndrome is characterized by hypophosphataemia, hypokalaemia, hypomagnesaemia and sodium retention. These severe electrolyte disturbances can lead to impaired cardiac, pulmonary and neurological function and are often hard to treat. By receiving energy predominantly from sugars, pancreatic insulin secretion is increased which induces uptake of electrolytes including phosphate and potassium, into cells. Furthermore, as protein synthesis is stimulated, increased production of adenosine tri-phosphate (ATP) leads to a higher cellular demand for phosphate.[^15^](#_ENREF_15) Although insulin secretion appears to be partially impaired in the early stages of refeeding, hypophosphatemia is a common feature during refeeding of malnourished children, and is associated with mortality.[^16-18^](#_ENREF_16)

In this trial, we aim to evaluate the outcome of using a revised formulation of F75 milk with reduced carbohydrate composition and without lactose, compared to the current formulation of F75 during the initial stabilisation period amongst children with severe acute malnutrition. In the new formulation, more will be provided by lipids and the total energy provided will be unchanged. The trial will be undertaken in two hospitals in Kenya and one hospital in Malawi.

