***Exclusion Criteria:***

- Declined to give informed consent
- Known allergy to milk products
- Any other reason the consenting investigator thinks that in the child’s best interests it inappropriate for them to take part.

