The parent or guardian will receive an explanation of the trial at admission and be given a chance to ask questions before written permission for their child to be included in the trial is sought by a member of the study team. It is recognised that in some cases, obtaining informed consent at admission for an acutely ill child may present challenges. Previous work on obtaining consent suggests a staged process.[^21^](#_ENREF_21) The validity of this has been assessed for use in cord blood collection in both Kilifi and Mombasa. (SSC Nos. 1215, 1778 & 1355). In situations where urgent feeding is needed, but it would be delayed by taking full informed consent, it is proposed to use a two phase consent process, where verbal assent for enrolment is taken by a clinician (appendix B) and later written consent (appendix C) is sought. If consent is refused at the second stage, any stored samples would be discarded and the child would receive standard care.

Field workers and clinical staff will be trained in administering the two stage consent procedure, following a standard operating procedure. Written consent will be taken by trained fieldworkers, recruited from the local population and fluent in the predominant local languages.

*iv. Confidentiality*

All records will be kept in a locked filing cabinet, which is accessed only by the investigators and the study nurse(s). No names will be recorded on the trial database. Every child will be allocated a unique identifying number which will be used as the linking identifier for databases. Only the investigators, the clinical monitor, the ethics committees or any other regulatory agencies will have access to the records. Every effort will be taken to maintain confidentiality. No information concerning the study or the data will be released to any unauthorized third party, without prior written approval of the sponsor.

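### For children enrolled on assent, written consent is timed by the event that is also the primary endpoint, so the chance of leaving the trial can depend on the outcome

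*Protocol*

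**What the plan says.** Four parts of the Protocol bear on this.

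- **Timing of consent.** Section 8, d) Procedures, Enrolment, says that to avoid delaying urgent feeding "assent for participation will be sought, and then written consent requested after the initial stabilisation". Section 11, iii. Informed consent, limits the two-stage process: "In situations where urgent feeding is needed, but it would be delayed by taking full informed consent". It places written consent only at some later point.
- **What the term means elsewhere.** Section 4 describes the comparison of the new formulation as "compared to the current formulation of F75 during the initial stabilisation period amongst children with severe acute malnutrition". Section 3 states that "the primary endpoint of the trial will be time to stabilisation (the end of the first phase of treatment for severe acute malnutrition", and section 8, Outcome measures, states: "The primary outcome is stabilisation, defined as having reached the second (transition) phase of treatment".
- **Who stays and who leaves.** Under Enrolment, if a child on assent "dies before written consent has been given, data and samples will be used for the study". Under Informed consent: "If consent is refused at the second stage, any stored samples would be discarded and the child would receive standard care". The exclusion criteria list "Declined to give informed consent" without naming a stage of consent.
- **Analysis.** Section 9(b) promises analysis by intention to treat, counts deaths before stabilisation as not stabilised, and plans a CONSORT flow diagram.

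**The concern.** A child enrolled on assent receives a study number, and with it an allocation, and starts the study milk before the parent gives written consent. If the consent time is read in the Protocol's own vocabulary, the parent is asked once the child has reached the primary endpoint. A child who dies first can no longer leave; a child who stabilises still can. Leaving after randomisation then depends on the outcome.

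The stored samples are directly at stake. The electrolyte and albumin changes to day 3, the faecal measures, pathogen detection, gut markers, microbiome and metabolite outcomes all rest on stored plasma or stool. Among children on assent, these samples are kept for early deaths and destroyed for survivors whose parents refuse. An analysis plan cannot restore discarded samples. If a site also removed the refusers' clinical data, the intention-to-treat analysis of the primary endpoint and of mortality would be affected too.

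**Working it through.** **Step 1. The Protocol's own figure.** Section 8, c) Sampling, gives 381 per arm for 50% versus 60% transitioned at day 5, α = 0.05 and 80% power. The Freedman log-rank formula, with two-sided α and with 0.50 and 0.60 entered as survival proportions, gives:

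- HR = ln 0.6 / ln 0.5 = 0.737 (inverse 1.357)
- events = (1.960 + 0.842)² × [(1 + 0.737)/(1 − 0.737)]² = 342.3, so 343
- per arm = 342.3 / 0.45 / 2 = 380.3, so 381

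The figure is reproduced and this point does not affect it. The target of 420 leaves room for 1 − 381/420 = 9.3% loss.

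**Step 2. The two rules side by side, for a child on assent.**

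| Course before written consent | Samples | Clinical data |
| --- | --- | --- |
| Dies | kept (stated) | kept (stated) |
| Asked, parent refuses | discarded (stated) | not stated |
| Taken home before being asked | not stated | not stated |

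**Step 3. Size for the primary endpoint.** The Protocol gives no refusal rate and no share on assent. Assume the worst case: every child is on assent, clinical data of refusers are removed, and only children stabilised by day 5 have been asked. With true day-5 proportion p and refusal r among the stabilised, the observed proportion is p(1 − r)/(1 − pr).

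| r, equal in both arms | 50% becomes | 60% becomes | Difference (points) | Kept per arm |
| --- | --- | --- | --- | --- |
| 2% | 49.5% | 59.5% | 10.0 | 416, 415 |
| 5% | 48.7% | 58.8% | 10.0 | 410, 407 |
| 10% | 47.4% | 57.4% | 10.1 | 399, 395 |

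With no true effect (50% in both arms) and refusal that differs by arm, a two-sided 5% test of the day-5 proportions behaves as follows:

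| Refusal by arm | Spurious difference (points) | Type I error |
| --- | --- | --- |
| 2% v 5% | −0.8 | 5.6% |
| 5% v 10% | −1.3 | 6.7% |
| 0% v 10% | −2.6 | 11.7% |

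This snapshot overstates the effect, because children who stabilise after day 5 are also asked later and some of them also leave. If 85% eventually stabilise (an assumption) and all of those are asked, the observed proportion is p(1 − r)/(1 − 0.85r). For 0% v 10% refusal this is 0.500 v 0.45/0.915 = 0.492, a difference of −0.8 points and a type I error of 5.6%.

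**Step 4. Size for mortality.** Take 420 per arm and assume 15% die before stabilisation (63) and 357 stabilise. Section 4 gives an overall case fatality of 10% to 30%, so the timing of those deaths is a further assumption. If refusers' data were removed, observed mortality would be 63/(420 − 357r): 15.0% at r = 0, 15.3% at 2%, 16.1% at 8% and 16.4% at 10%. If only 20% of children were on assent (again an assumption), refusal of 2% v 8% would give 63/(420 − 1.4) = 15.05% v 63/(420 − 5.7) = 15.2%.

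**The case against.** The strongest reply is that the consent sentence may not refer to the endpoint at all. It sits in a passage about urgent feeding to prevent hypoglycaemia. The Enrolment text treats death between assent and written consent as uncommon, which fits poorly with a wait until transition when case fatality is 10% to 30% and highest early in treatment, unless few children are on assent. The instruction that a refuser's child moves to standard care also makes most sense while the child is still on study milk. This part of the objection stands: a short emergency interval may well be meant. It does not remove the point, because the text then uses the endpoint's name for something else, and sites are left to guess.

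Three stronger readings are tempting, and the documents do not support them.

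- **That refusers' clinical data are dropped by rule.** The refusal rule names only stored samples. The consent exclusion criterion is an entry criterion, and the intention-to-treat statement and CONSORT diagram point towards keeping randomised children.
- **That losses can never occur among deaths.** A child who dies after the parent has been asked could already have left by refusal, so this fails for mortality until discharge.
- **That about half of children on assent still lack written consent on day 5.** This follows from the 50% transition figure only on the literal reading of the consent time, which other wording undercuts.

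It is also fair that refusal differing by arm is conjecture. The trial is double-blind, with identical packaging and very similar taste, and nothing in the Protocol links refusal to tolerance. The opposite cannot be assumed either, since parents would decide after experience of the milk, and the Protocol itself expects that stools may differ.

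**Conclusion.** The point holds in a limited form. Read in the Protocol's own terms, the second-stage consent time coincides with the primary endpoint. Combined with the rule that keeps early deaths and the rule that discards refusers' samples, this makes the chance of leaving depend on the outcome. The loss is explicit for stored plasma and stool, and possible but unstated for clinical data. The Enrolment and Informed consent sections must be reconciled on what interval is meant.

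The size cannot be established, because the share on assent and the refusal rate are not given. Even if every child is on assent and refusers' clinical data are removed, equal refusal of 2% to 10% leaves the primary contrast at 10.0 to 10.1 points with 395 to 416 children per arm, above the 381 required. Bias between arms needs refusal that differs by arm. It is small for modest gaps, and the 11.7% type I error at 0% v 10% is an extreme case under the least favourable assumptions. All effects shrink with the share on assent. This is a cheap improvement; a reader might take it for a flaw that invalidates the primary analysis, and the documents do not support that.

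**What to change.** 1. Under Enrolment, replace the present consent time with one set independently of the endpoint, for example a fixed short time after enrolment and before the day-3 samples.
2. Align Enrolment with Informed consent: assent is used only where full consent would delay urgent feeding.
3. At second-stage refusal, ask separately for permission to keep data already collected. Where it is given, analyse the child as randomised. Where it is not, show the child by arm in the CONSORT flow as randomised and withdrawn, and not as an ineligible child.
4. State the rule for a child who leaves hospital before the parent has been asked, and report second-stage refusals by arm.

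The cost is a wording amendment to the Protocol and the consent procedure, plus one extra line on the consent form. The downside is small: some parents will be approached while the child is still ill, which may slightly raise refusals. The change is best made before recruitment, because discarded samples cannot be recovered.
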